#### 4.5 Trial drug distribution and dispensing

Both the trial drug and light source are provided by Shanghai Fudan-Zhangjiang Bio-Pharmaceutical Co., Ltd. and delivered to all study centers periodically per the protocol by the company's clinical study monitors. The drugs are distributed by a special person at each study center. The observation doctors should dispense the drugs by the order of each patient's visit and the sequence of drug numbers without choosing the drugs intentionally. The drug numbers remain unchanged throughout the trial process. After successful enrollment, the patients will be offered with sufficient dose of trial drug of identical labels.

The drug managers should fill out the drug dispensing/recovery registration form timely and accurately.

An emergency letter should accompany each of the trial drugs and the letters will be maintained by the principal investigator of the participating institution.

#### 4.6 Drug counting

The investigators should accurately record the dose of each medication (bottle).

#### 4.7 Drug storage

The study drug should be stored under 2~8°C away from light in a special refrigerator, which should be locked and maintained by a special person. The investigators should return all the unused drugs to the monitors of Shanghai Fudan-Zhangjiang Bio-Pharmaceutical Co., Ltd. at ending of this trial.

#### 4.8 Concomitant drugs

The subjects are not allowed use the drugs listed in the exclusion criteria during this trial. If concomitant drugs is indeed needed to treat other diseases, the name, dosage, indication, the beginning and ending date, and other relevant information should be recorded in the case report form (CRF).

#### 5. The total number of subjects, grouping, randomization method and the tasks undertaken by each center

The total number of subjects planned to include is 440 and the distribution of these subjects among the centers are listed in the following table:

| Centre No. / Clinical study institution                                                    | Trail group | Control group | Total |
|--------------------------------------------------------------------------------------------|-------------|---------------|-------|
| 1. Peking University First Hospital                                                        | 39          | 13            | 52    |
| 2. Institute of Dermatology, Chinese Academy of Medical Sciences                           | 39          | 13            | 52    |
| 3. The Ninth People's Hospital of Shanghai Jiaotong University School of Medicine          | 57          | 19            | 76    |
| 4. Guangzhou General Hospital of Guangzhou Military Region                                 | 39          | 13            | 52    |
| 5. Huashan Hospital of Fudan University                                                    | 39          | 13            | 52    |
| 6. Xijing Hospital of the Fourth Military Medical University                               | 39          | 13            | 52    |
| 7. Union Hospital of Tongji Medical College, Huazhong University of Science and Technology | 39          | 13            | 52    |
| 8. Xiangya Hospital of Central South University                                            | 39          | 13            | 52    |
| Total                                                                                      | 330         | 110           | 440   |

The number of subjects can be adjusted according to the inclusion rate at each center.

#### 6. Trial arrangement

- Treatments: up to 2 times (the patients can receive an additional treatment if the treatment area did not subside completely after the first treatment)
- Efficacy evaluation: the efficacy evaluation is carried out in Week 8 after each treatment; both

evaluations are compared to the disease conditions before the treatment.

- Laboratory examination: the testing is carried out before each treatment and on Day 4 after the treatment.

Trial Flowchart

|                                   | PDT treatment                 |       |                                |       | Efficacy observation                                        |
|-----------------------------------|-------------------------------|-------|--------------------------------|-------|-------------------------------------------------------------|
|                                   | The first course of treatment |       | The Second course of treatment |       | The first/second course of treatment
Week 8 of treatment |
|                                   | Day 1                         | Day 4 | Day 1                          | Day 4 |                                                             |
| Instructions for patients         | ×                             |       |                                |       |                                                             |
| Signing ICF                       | ×                             |       |                                |       |                                                             |
| Laboratory examination            | ×                             | ×     | ×                              | ×     |                                                             |
| Inclusion criteria                | ×                             |       |                                |       |                                                             |
| Exclusion criteria                | ×                             |       |                                |       |                                                             |
| History                           | ×                             |       |                                |       |                                                             |
| Accompanied diseases              | ×                             |       |                                |       |                                                             |
| Therapies                         | ×                             |       |                                |       |                                                             |
| PWS type                          | ×                             |       |                                |       |                                                             |
| Photography of the treatment area | ×                             | ×     | ×                              | ×     | ×                                                           |
| Allocation of drug numbers        | ×                             |       |                                |       |                                                             |
| PDT treatment                     | ×                             |       | ×                              |       |                                                             |
| Observation of photoreaction      | ×                             | ×     | ×                              | ×     | ×                                                           |
| Observation of adverse event      | ×                             | ×     | ×                              | ×     | ×                                                           |
| Evaluation of efficacy            |                               |       | ×                              |       | ×                                                           |
| Investigator's evaluation         |                               |       | ×                              |       | ×                                                           |
| Subject's evaluation              |                               |       | ×                              |       | ×                                                           |
| Changes of concomitant therapies  |                               | ×     | ×                              | ×     | ×                                                           |

## 7. Observation of the subjects

- ☞ Observation and evaluation of the same subject should be carried out and recorded carefully by the same investigator as far as possible.
- ☞ The treatment area of all patients should be photographed before and after the treatment at each visit. The sponsor will provide uniform labels to mark the subject's number, date, and number of treatments on the photograph.

7.1 The patient's general conditions (including the initials, date of birth, body height, body weight, vital signs, etc.), other comorbidities and history of treatment, and the onset history of port-wine stains (including past medical history, course of disease, affected sites, areas, treatments, etc.) are recorded at enrollment.

7.2 typing type of port-wine stains in the lesion area should be assessed at enrollment

Based on the erythema color and skin hyperplasia, port-wine stains can be divided into three types:

- Red type: the lesion is flat, not raised, similar to normal skin, the color is light pink to dark red and fades completely on finger pressing.
- Purple type: the lesion is flat, not raised, similar to normal skin, the lesion is pale to dark purple and the color can fade completely or incompletely.
- Hypertrophic type: the lesion is thickening and raised above normal skin with nodular hyperplasia, the color is dark purple-red and fades completely or incompletely.

7.3 Laboratory examination: all subjects should receive the following examinations:

- Routine blood tests: Included WBC, RBC, HGB, PLT.
- Routine urine tests: including urine proteins and urine glucose, WBC, RBC.
- Blood biochemical tests: Included ALT, AST, BUN, CR, TBiL.
- ECG recording:
- Urine pregnancy test (only for female patients of childbearing age without using contraceptive measures)

7.4 Observation of concomitant drug: record the name, indication, dosage, route of administration, start and end date of the concomitant drugs used by patients during their participation in this clinical study.

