### 3.5 Subject selection

#### 3.5.1 Inclusion criteria

All the patients participating in this clinical study must satisfy all the following criteria:

- The patients must be clinically diagnosed as port-wine stains;
- Male or female patients aged 14~65 years;
- The patients have read the subject's instructions and are willing to receive the treatment per protocol requirements and complete the visits in timely manner;
- The patients agree to sign the written informed consent form (ICF);
  - ✧ For subjects aged <18 years, both the subjects and legal guardians should sign the ICF at the same time.

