#### 3.5.2 Exclusion criteria

The patients who meet any one of the following criteria must be excluded from this clinical study:

- The affected area has other concomitant skin diseases (e.g. severe acne, contact dermatitis, or purulent infection) that may affect the efficacy evaluation;
- The treatment area has been treated with isotope therapy, PDT or other therapies that may affect the efficacy evaluation;
- The patients are currently suffering from allergic diseases; the patients have known photosensitive dermatitis and porphyria or known history of allergies to the trial drug (porphyrins) and drugs with similar chemical structure;
- The patients have allergic constitutions, scarring constitutions or scarring tendency;
- The patients used known photosensitive drugs such as griseofulvin, thiazide diuretics, sulfonylureas, phenothiazines, sulfonamides, retinoic acids, quinolones and tetracyclines within 1 month
- The patients have known severe immunocompromised conditions or require long-term use of corticosteroids and immunosuppressants;
- The patients have ECG abnormalities and organic heart diseases;

- Abnormal liver function (ALT and AST exceed the upper limit of normal (ULN), TBIL exceeds 1.5xULN) or severe renal dysfunction (renal function index exceeds 1.5xULN);
- The patients have hereditary or acquired coagulation disorders or are using anticoagulants;
- The patients have severe neurological, mental and endocrine disorders;
- The patients received systemic therapies to treat port-wine stains within 4 weeks prior to this treatment;
- The patients received topical therapies to treat port-wine stains within 2 weeks prior to this treatment;
- Pregnant and lactating women or women using inappropriate contraceptive measures;
- The patients participated in other drug clinical trials within 4 weeks prior to this treatment.

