- 5) Precautions: the patients should be instructed to observe the photoreaction after drug infusion and pay attention to photo protection. The photoreaction is expected to disappear completely in approximately 10 days after drug infusion. During the light protection period (2 weeks), the subjects should pay attention to protection of the exposed skin and eyes, avoid irradiation of sunlight or strong indoor lights. In case of drug extravasation during the infusion, the extravasation area must be kept completely away from light for a fairly long time until local swelling and discoloration disappears completely, otherwise severe local skin photoinjury may occur.
- 6) PDT may cause the following treatment reactions: the patients may experience itching, burning sensation, pain, swelling, blisters and scabs at the irradiated and surrounding area. These therapeutic responses are usually transient and self-healing without special treatment.
- 7) Adverse reactions: If light protection measures are not taken properly, some patients may experience photosensitive reactions such as photosensitive dermatitis, photosensitive ophthalmia, photosensitive cheilitis, etc; some patients may experience nausea, dizziness, headache, drowsiness, total bilirubin elevation, hyperpigmentation, hypopigmentation,

treatment site infection, scarring and other adverse reactions.

- 8) At week 8 after the first treatment, if the color of treatment area has not subsided completely and there are no serious pigmentation, scarring and other conditions that are unsuitable for re-treatment according to the investigator's judgment, the next stage treatment can be carried out.

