### 9.3 Severe adverse events (SAE) and unexpected adverse drug reactions (UADR)

9.3.1 Definition: SAE is one of the adverse events below and might occur at any doses:

- ✧ Causing death
- ✧ Life-threatening
- ✧ Requiring hospitalization or prolonged stay in hospital
- ✧ Causing long-term or significant disability, or affecting working and living capabilities
- ✧ Causing congenital malformations

“UADR” refers to an adverse reaction, the nature or severity of which is not consistent with the applicable product information.

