### 10.2 Common causes for subject's withdrawal

#### 10.2.1 Withdrawal decided by the investigators

When it is no longer appropriate for the subjects to continue trial as a result of trial-emerged situations, the investigators can decide the withdrawal of the subject from this trial. The common reasons are as follows:

- ✧ A subject discrepant with the inclusion criteria were included by mistake
- ✧ Allergic reactions or disease deterioration which need emergency measures
- ✧ Poor compliance of a subject, who fails to use the study drug per requirements, and violate the trial protocol
- ✧ In the investigator's opinion, continuing the treatment is not to the patient's best interests (e.g. pregnancy)
- ✧ The efficacy can't be evaluated or the efficacy or safety evaluation is affected by reasons like data incompleteness, etc
- ✧ Unblinding or emergency unblinding
- ✧ It is inappropriate for the subjects to continue this trial due to AE or SAE

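### Women who are eligible because they use contraception have no required pregnancy test before either treatment

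*Protocol*

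**What the plan says.** The inclusion criteria (Protocol 3.5.1) admit "Male or female patients aged 14~65 years". The exclusion criteria (3.5.2) bar "Pregnant and lactating women or women using inappropriate contraceptive measures".

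Section 7.3 lists the laboratory examinations for all subjects, but its own parenthesis narrows the urine pregnancy test: "only for female patients of childbearing age without using contraceptive measures". Section 6 fixes the timing of the laboratory work: "the testing is carried out before each treatment and on Day 4 after the treatment".

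The flowchart in section 6 marks the exclusion criteria on Day 1 of the first course only. Before the second course, section 4.3 item 8 sets the condition for re-treatment, which begins "At week 8 after the first treatment, if the color of treatment area has not subsided completely" and also asks the investigator to judge that nothing makes re-treatment unsuitable.

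Pregnancy appears once more in section 10.2.1, as the example of a case where "continuing the treatment is not to the patient's best interests (e.g. pregnancy").

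**The concern.** The testing rule works against the eligibility rule. Pregnancy is an exclusion that a simple test can verify, and the protocol already includes that test. Yet the test is not required in the women of childbearing age whom the contraception criterion lets in. Contraceptive methods fail and are sometimes used irregularly, so use of a method does not establish that a woman is not pregnant on the day of infusion.

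What is at stake is exposure of an unrecognised pregnancy to an intravenous photosensitiser, at either of two treatments. The protocol itself regards pregnancy as a reason to keep women out and to withdraw them. Its general SAE definition (9.3.1) also includes "Causing congenital malformations", although that is a standard criterion and no evidence of a known hazard of this drug. This is a patient-safety matter and does not bear on the efficacy inference.

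**Working it through.** No statistical calculation applies. The check sets the eligibility rule, the testing rule and the visit schedule side by side and counts.

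**Who is tested, compared with who is eligible.** The exclusion criterion does not say whether using no contraception counts as inappropriate contraception, so both readings were tried.

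| Reading of 3.5.2 | Women using no contraception | Women using appropriate contraception |
|---|---|---|
| No contraception counts as inappropriate | Excluded, yet the only group for whom the test is required | Eligible, no test required |
| Some may enrol without contraception (for example, if abstinent) | Eligible, tested | Eligible, no test required |

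The right-hand column is the same under both readings. Under the first, almost no eligible woman of childbearing age would be tested at all.

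**Required tests per contraceptive user.**
- Scheduled laboratory examinations: 2 courses × 2 (Day 1 and Day 4) = 4.
- Examinations that precede a treatment: 2 courses × 1 = 2.
- Required pregnancy tests: 0 of 4 overall. The count that matters is 0 of the 2 before treatment.

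**Checks before course 2.**
- Exclusion criteria are scheduled on 1 of 2 treatment days (flowchart, section 6).
- Interval from that review to the week 8 decision on course 2: 8 weeks × 7 = 56 days.
- A woman known to have stopped contraception by then would fall within the 7.3 rule and be tested.
- The flowchart row "Changes of concomitant therapies" is marked on Day 1 of course 2 and could reveal that a contraceptive drug had been stopped.
- An unreported lapse in a non-drug method, or failure of a method still in use, would be found by neither.

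Under section 3.1 the control group receives placebo in course 1 and active drug in course 2. Women in that group therefore first meet hemoporphin at the treatment that has no scheduled exclusion review.

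**What cannot be computed.** The protocol gives no expected sex split, no contraception data and no reproductive-toxicity data. Neither the number of women affected nor the fetal risk can be derived from it.

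**The case against.** The best defence is that this is a deliberate, risk-based rule: test women with no contraceptive protection, and rely on history in those who have it. That is coherent if some women without contraception may enrol. If they may not, the rule tests mainly women who are already excluded, and the defence weakens.

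It can also be said that course 2 has more safeguards than the exclusion row of the flowchart suggests. Item 8 of section 4.3 lets the investigator judge a subject unsuitable for re-treatment, section 10.2.1 names pregnancy as a ground for withdrawal, and adverse events are sought at every visit by inquiry and examination. This is fair, and the single scheduled exclusion review should not be read as the only check. But these safeguards act on a pregnancy that is known or suspected, and the gap concerns one that is not.

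Two further points stand as limits. The protocol does not forbid testing contraceptive users, so centres may do it as routine. The consent form and subject instructions are not in the text reviewed and may set contraception or reporting duties. Neither replaces a required test.

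**Conclusion.** The concern holds. As written, a woman of childbearing age who uses appropriate contraception has 0 of 2 required pregnancy tests before treatment, whichever way the exclusion criterion is read. The remaining gap is narrow: an unrecognised pregnancy from method failure or an unreported lapse, at either treatment. Its frequency and consequences are unknown from the document.

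The conclusion rests on the explicit restriction in section 7.3 and on no other section requiring the test. It assumes only that some women of childbearing age enrol while using contraception, which the age range and the exclusion wording allow. The change should be made because it improves safety at very small cost, not because the trial's validity depends on it.

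**What to change.** In section 7.3, delete the last four words of "only for female patients of childbearing age without using contraceptive measures" and state that a negative urine pregnancy test is required before each treatment in all female subjects of childbearing age. Say that the Day 4 laboratory examination need not repeat it.

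The cost is at most 1 test × 2 treatments = 2 extra urine tests per contraceptive user. The test is already in the protocol, laboratory examinations already precede each treatment, and routine urine is already collected at them. No visit is added, and the sample size, randomisation and analysis do not change.

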## 8. Efficacy evaluation

### 8.1 Primary efficacy

The expert panel will determine the efficacy based on the photos taken before and after treatment per the following criteria.

- Almost cured: color of the treated area subsided basically (the level of improvement  $\geq 90\%$ );
- Significantly improvement; color of the treated area subsided obviously (the level of improvement  $\geq 60\%$ ,  $< 90\%$ );
- Some improvement: color of the treated area subsided partially; (the level of improvement  $\geq 20\%$ ,  $< 60\%$ );
- No improvement: color of the treated area did not change essentially. (the level of improvement  $< 20\%$ );

8.2 The investigators and patients will subjectively evaluate the efficacy as excellent, good, moderate and insufficient and safety as excellent, good, moderate and unsatisfied, separately.

## 9. Safety

9.1 The adverse events (AE) are identified through inquiries of the subjects (caution: avoid inductive questioning, phrases such as "how do you feel after the treatment?" can be used during the inquiry), physical examination and comparisons of the laboratory examination results before and after the treatment including blood routine, urine routine, liver function, kidney function, ECG recording.

